## Assignment of interventions

### Sequence generation

In order to ensure allocation concealment, balance and to minimize bias, randomization will be performed by a third-party biostatistician at the George and Fay Yee Centre for Health Innovation. Randomization will be performed using code written in the R statistical programming language (Versions 3.5.3). Treatments will be assigned with a 1:1 ratio of liberalized dK then standard dK or standard dK then liberalized dK, stratified by sex, with random block sizes of 2.

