### Trial design

This study is an open-label, randomized 2-period crossover definitive superiority trial. The study will be sixteen weeks in duration. Thirty male and female individuals living with CKD will be recruited, with a minimum 40% of each sex. Participants will be randomized to receive both restricted (standard care) and liberalized (experimental) K content fruit and vegetables for six weeks.

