### Concealment mechanism

Allocation to intervention group will be perfomed by a trial coordinator using a secure, web-based REDCap tool hosted at the University of Manitoba using the tables created in R. To minimize bias, intervention assignments will not be released until run-in period completed.

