### Implementation

The study biostatistician will generate the allocation sequence and assign participants to the interventions. The study coordinator will enroll the participants.

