### Blinding

Assessors who will be completing all assessments will be blinded to the intervention assignment. We will ask participants not to communicate their intervention to the assessor. Blinding of the participants and study staff is not possible given the nature of the intervention, but the study statistician and the entire data management team will be blinded to allocation during analysis.

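### The single block size of 2 lets 14 or 15 of the 30 sequence assignments be deduced before release, so the concealment claimed is only partly achieved

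*Protocol article*

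**What the plan says.** Everything here is in the protocol article.

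- **Sequence generation** gives the aim: "In order to ensure allocation concealment, balance and to minimize bias, randomization will be performed by a third-party biostatistician". It gives the ratio, "Treatments will be assigned with a 1:1 ratio of liberalized dK then standard dK or standard dK then liberalized dK", and the blocking, "stratified by sex, with random block sizes of 2". No second block size appears anywhere, and nothing says that the size is kept from site staff.
- **Trial design** calls the study open-label, and **Blinding** adds: "Blinding of the participants and study staff is not possible given the nature of the intervention".
- **Concealment mechanism** says who allocates: "Allocation to intervention group will be perfomed by a trial coordinator using a secure, web-based REDCap tool". It adds one safeguard, that an assignment is released only when the run-in is complete.
- **Implementation** says "The study coordinator will enroll the participants", but also gives the task of assigning participants to the study biostatistician, which does not agree with Concealment mechanism.

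**The concern.** A block size can be random only if there is more than one to choose from. With 2 as the only size, what varies is the order within each pair. At 1:1, a pair holds one of each sequence, so the second same-sex participant of a pair receives whatever the first did not.

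The stated safeguards do not address this. The outside statistician and REDCap protect the list from being read, but not from being deduced. Holding back a participant's own assignment until the run-in ends does not help either, because the earlier same-sex assignment has by then been released and is visible to unblinded staff.

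Judgement is still exercised between enrolment and randomization: the safety assessment one week after baseline, and the investigator's discretion to discontinue a participant. If the coming order is known, these decisions could be influenced by it, and the two sequences could then differ in the kind of participant they contain.

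Order can matter to the result in two ways. A participant withdrawn in the first period, for instance for hyperkalaemia risk or for starting a potassium binder, is never observed on the second diet, and Statistical methods excludes participants with missing values for a required variable. Period effects that differ between kinds of participant are the other route.

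**Working it through.** The plan gives no figure for predictability, so there is none to reproduce.

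**Inputs.** Block size 2, ratio 1:1, strata by sex (Sequence generation). N = 30 with at least 40% of each sex (Trial design), so at least 0.40 × 30 = 12 and at most 18 per stratum.

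**1. Assignments that can be deduced.** In each sex every second assignment is fixed, so the count is floor(n_F/2) + floor(n_M/2):

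| Sex split | Deducible | Share of 30 |
|---|---|---|
| 12/18 | 6 + 9 = 15 | 50% |
| 13/17 | 6 + 8 = 14 | 47% |
| 14/16 | 7 + 8 = 15 | 50% |
| 15/15 | 7 + 7 = 14 | 47% |

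The table is the same with the sexes exchanged.

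**2. Overall guessing.** At 15/15 each sex has 8 first-of-pair assignments (guessed with probability 1/2) and 7 certain ones: (8 × 0.5 + 7)/15 = 11/15 = 73% correct. In complete blocks it is (0.5 + 1)/2 = 75%. Full concealment gives 50%.

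**3. Comparison with other schemes.**

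- *Fixed block of 4, size known.* Of the 6 possible orders, 2 (AABB, BBAA) leave two assignments determined and 4 leave one: (2 × 2 + 4 × 1)/6 = 4/3 per block of 4, or 1/3.
- *Blocks of 2 and 4, equally likely.* If the sizes are withheld, no assignment can be deduced with certainty. If the two sizes leak but not the block boundaries, only an AABB or BBAA block gives itself away, and its last two assignments are then certain: 1/2 × 1/3 × 2 = 1/3 per block, with mean block length (2 + 4)/2 = 3, so 1/9 (11%) in the long run.
- *Guessing the under-represented sequence* under the 2-and-4 mix was simulated (20,000 runs, 15 per sex) and is right about 71% of the time, against 73% with blocks of 2.

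Varying the size therefore removes most of the certainty but little of the general guessability.

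**4. Balance.** Blocks of 2 allow a difference of at most 1 per sex, so at most 2 overall (16 v 14). Blocks of 2 and 4 allow at most 2 per sex, so at most 4 overall (17 v 13).

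**5. What imbalance costs.** In a paired comparison without a period term, an additive period effect p shifts the treatment estimate by p × (difference in sequence sizes)/30: 2/30 = 0.07p at 16 v 14 and 4/30 = 0.13p at 17 v 13. With period in the model this shift is removed.

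**The case against.** The strongest reply is that this is a crossover with, in essence, a paired analysis. Only the order can be predicted, and each participant's own potassium level cancels from the contrast. Placing people with higher potassium in one sequence does not by itself bias the result; that needs order-related dropout, carryover, or a period effect that differs with the characteristic. This stands, and it limits the size of the concern. It does not close the dropout route.

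Several further points also stand.

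- Consent and enrolment come two weeks before randomization, the run-in has a fixed length, and the eligibility range for potassium is numeric. Exchanging two participants' places needs another of the same sex ready at about the same time, which will be uncommon at one enrolment per week.
- Assessors are to be blinded, the statistician is blinded during analysis, and the primary outcome is a laboratory value.
- Because Concealment mechanism and Implementation disagree on who assigns, it is not settled who sees past assignments.
- Tight balance is a fair reason for small blocks in 30 people, and Sequence generation names balance as an aim. Blocks of up to 6 could give a difference of 3 per sex, or 18 v 12 overall, which is why smaller sizes are suggested below.

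Finally, the phrase may be a slip in a condensed article. If it stands for randomly permuted blocks of 2, the problem is the same. If other sizes were omitted, the statement is wrong and needs correcting.

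**Conclusion.** The point holds, with limited consequence. As written, the scheme is a fixed block of 2 within each sex, and 14 or 15 of 30 sequence assignments (47-50%) can be deduced before release. Concealment is thus achieved for about half of the assignments. This assumes that the written size was the one used, and that someone involved before randomization knows both the size, which the article publishes, and the earlier same-sex assignments.

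A reader might infer three stronger things that the documents do not support:

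- *That concealment fails altogether.* The first assignment of each pair remains unpredictable.
- *That the sequences would become unequal in number.* Blocks of 2 hold them to 16 v 14 at worst; only their composition can be skewed.
- *That the potassium comparison is biased.* Nothing shows that any assignment was steered. The figures above count predictable assignments and do not measure bias in serum potassium, for which the documents give no basis. Any such bias should be smaller than in a parallel trial.

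The change is still worth making, because the text claims a protection that it does not deliver and the repair is cheap.

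**What to change.** - In Sequence generation, specify permuted blocks of randomly varying small size (for example 2 and 4), stratified by sex, with the sizes known only to the third-party statistician and left out of documents that site staff can see.
- Regenerate the part of the REDCap table that has not been used.
- Reconcile Concealment mechanism with Implementation, so that one role performs the assignment.
- If allocation is already complete with blocks of 2, correct the wording and report the predictability as a limitation. If other sizes were in fact used, correct the wording.

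The cost is a few lines of R and one upload, plus looser balance: up to 2 per sex and 4 overall (17 v 13), instead of 1 per sex. Including period in the mixed model removes the effect of that imbalance on the treatment estimate; the analysis plan, which is not shown, may already include it.

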### Concealment mechanism

Allocation to intervention group will be perfomed by a trial coordinator using a secure, web-based REDCap tool hosted at the University of Manitoba using the tables created in R. To minimize bias, intervention assignments will not be released until run-in period completed.

### Implementation

The study biostatistician will generate the allocation sequence and assign participants to the interventions. The study coordinator will enroll the participants.

### Blinding

Assessors who will be completing all assessments will be blinded to the intervention assignment. We will ask participants not to communicate their intervention to the assessor. Blinding of the participants and study staff is not possible given the nature of the intervention, but the study statistician and the entire data management team will be blinded to allocation during analysis.

## Data collection, management and analysis

### Data collection methods

Data will be entered into REDCap database on a secure REDCap server housed by the University of Manitoba. Routine data management audits and data quality checks will be conducted by individuals in the Data Management group at the George and Fay Yee Centre for Health Innovation.

All research records will be kept for 10 years. After 10 years, paper files will be disposed of using the confidential document destruction method at the Chronic Disease Innovation Centre. The electronic data that will be obtained from the trial will be retained and de-identified for a total of 10 years once the study has been completed. The electronic trial data that was obtained from the trial may be utilized in academic journals for publication, however the data will be in shared in a de-identified format. Additionally, the electronic data may potentially be stored by open-access repositories or academic journals under an open access policy which may allow different research teams to access the data for research purposes and further data analysis [16].

### Data Management

A unique numerical coding system that will not contain any direct identifiers, such as name or initials to de-identify the data collected in this study. Data will be entered into REDCap database on a secure REDCap server housed at University of Manitoba. The Data Coordinating Centre that is located within the Data Science group at the Centre for Healthcare Innovation will be taking on the REDCap database data management. They will also be conducting regular data quality checks to ensure data is well kept. A unique code will be utilized for input into the study database for all research data collected throughout the duration of the trial. To ensure the following of site protocols, all research records will be kept for 10 years, following the 10 years, the confidential document destruction method will be used to dispose of any paper files [16]. Additionally, electronic data will be retained and de-identified for 10 years once the trial has been completed.

### Statistical methods

The primary analysis will be based on sK concentration, comparing the endpoints of the intervention periods. The effects of treatment on primary and secondary outcomes using a linear mixed-effects model for the repeated measures will be examined (essentially a paired comparison of the endpoints of the standard care dK diet versus the experimental dK diet). Sex will be included in this model as a fixed factor. Model assumptions for outcome data will be verified by visual inspection of residual plots and through sensitivity analyses regarding missing value strategies. Outcomes which appear to violate the modelling assumptions may be transformed prior to analysis or analysed using another, more appropriate model (e.g., generalized linear mixed models) in supportive analyses. Demographic data will be reported as the mean ± standard deviation. Analyses of the secondary outcomes will be reported as unadjusted and adjusted (expected marginal) means with 95% confidence intervals.

The primary analysis will be conducted using the All Participants (intent to treat) analysis set. The primary analysis will be repeated in the Completers analysis set. Demographics and all other baseline measurements will be analyzed in the All Participants set as well as in the Completers set.

The number and proportion of missing values will be documented in the clinical study report. Missing values will not be imputed unless otherwise noted. Analyses will exclude data from participants who have missing values for any variable required for the analysis. When data are observed to be unusual in a way that cannot be explained or ruled to be in error, analyses may be repeated after excluding the record involved. These additional analyses will be presented as sensitivity analyses. Additionally, all protocol deviations documented in the clinical trial database will be tabulated (if appropriate) and listed in the clinical study report. In general, analyses resulting in p-values less than 0.05 will be described as statistically significant, without adjustment for multiple inference. All results arising from secondary, exploratory and supportive analyses will be identified as such. Overall, the analysis done in this trial is the similar to the ReDACKD clinical trial [16].

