## Interventions

### Intervention descriptions

Once the baseline, run-inand safety assessments have been completed, participants will be randomized into one of the two interventions:

*Liberalized dK + via fruit and vegetables (Experimental group)*.

This group will receive weekly supplementation of higher K fruit and vegetables via home delivery during the liberalized dK run in and treatment period. The weekly deliveries will contain combinations of fresh, frozen and dried fruit and vegetables, as well as juices and low-sodium soups which have been selected for their K content and shelf-life. Contents may vary throughout the intervention period based on price and availability. Participants will receive weekly deliveries of K rich fruit and vegetables that contain more than 250 mg of K per 100 g serving, such as potatoes, legumes, beets, carrots, oranges and pears. prior to the run-in week, participants will receive a 30-60-minute counseling session from the study registered dietitian (RD), where they will be instructed to incorporate the fruit and vegetables into their diet targeting a daily dK intake of 2000 mg from the delivered fruit and vegetables over 3 to 4 meals, and a daily dK intake of approximately 3500 mg. During this counseling session from the study RD standard renal diet with instructions to avoid none fruit and vegetable sources of dK will be reinforced, but not the preparation of vegetables to reduce dK content.

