### Outcomes

The primary outcome is evaluating sK concentration during the five timepoints at week 0, 1–2, 8, 10 and 16. The secondary outcomes include assessing health related quality of life through KDQOL-SF and STS5 which will be assessed throughout the trial, analyzing clinical chemistry systolic and diastolic blood pressure, and assessing dietary data using the information received from ASA24. Clinical chemistry will look at sodium, potassium, urea, phosphate, and the albumin/creatinine ratio in the urine alongside the collection of blood samples for serum potassium, hemoglobin A1C, albumin, bicarbonate, calcium, chloride, creatinine, eGFR, glucose, phosphorus, sodium and blood urea nitrogen measurement. All samples will be collected and processed by the Diagnostic Services of Manitoba. Individuals will be scheduled for an in-person visit which will include a clinical exam and blood sample to monitor serium potassium and bicarbonate during weeks 1 or 2. Secondary outcome measures will be measured on week 0, 8, 10 and 16. Additionally, anthropometric measurements such as height, weight and BMI will be collected at baseline alongside blood pressure in triplicate.

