### Participant timeline

See Appendix A.

For the first two weeks, all participants will start on a liberalized potassium run-in period. Following the run-in period, the participants will be randomized to either the experimental group or the standard care group for six weeks. After the six weeks, a crossover will occur after a two-week washout period.

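### The primary crossover model names sex but not period; a period term costs one degree of freedom and protects the diet comparison if the two periods differ

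*Protocol article*

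**What the plan says.** The design is an "open-label, randomized 2-period crossover definitive superiority trial" (Trial design). Allocation to the two diet orders is 1:1, "stratified by sex, with random block sizes of 2" (Sequence generation).

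On the schedule, the Participant timeline states "For the first two weeks, all participants will start on a liberalized potassium run-in period". Randomization and the first six-week diet follow. Then: "After the six weeks, a crossover will occur after a two-week washout period".

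On the analysis, Statistical methods bases the primary comparison on serum potassium at the ends of the intervention periods. It specifies a linear mixed-effects model for repeated measures, glossed as "essentially a paired comparison of the endpoints of the standard care dK diet versus the experimental dK diet", and adds: "Sex will be included in this model as a fixed factor". No period or sequence term appears anywhere in the article. Missing values are not imputed, and participants lacking a required value are left out. Under the discontinuation criteria, only withdrawals in the first two weeks are replaced.

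Elsewhere the response is worded differently. The Outcomes section says "The primary outcome is evaluating sK concentration during the five timepoints at week 0, 1–2, 8, 10 and 16", and the hypothesis under Objectives speaks of change in serum potassium.

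**The concern.** In a two-period crossover, each person's diet difference also contains the difference between the periods, with opposite sign in the two sequences. A comparison that ignores period leaves that component in the residual. If the two sequences contribute unequal numbers, it also leaves part of it in the diet estimate.

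The one covariate the article names cannot help with this. Sex takes the same value at both endpoints, so as a main effect it drops out of the contrast for anyone with both values. Including it is reasonable because it is the stratification factor, but it does not do the work of a period term.

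The schedule gives some reason to allow for a period difference, because the periods are entered from different conditions. At stake are power, where the stated 80% has little slack, and protection against a modest bias if losses after the run-in fall unevenly.

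**Working it through.** **Inputs from the article.** N = 30 (Recruitment); target difference 0.35 mEq/L and within-subject SD 0.46 (Sample size); significance at 0.05 (Statistical methods), taken as two-sided because sidedness is not stated.

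**Assumption.** The article gives no period difference π, so 0.1, 0.2 and 0.3 mEq/L are used as a range.

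**1. The article's own figure.** SD of the paired difference = 0.46 × √2 = 0.651. Standard error = 0.651/√30 = 0.119. The noncentral t with 29 df gives power 81.3%, and the smallest N for 80% is 30. The stated 80% reproduces.

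**2. What period does to the paired difference.** With diet effect τ, the liberalized-minus-standard difference has mean τ + π in one sequence and τ − π in the other. Ignoring sequence at 15/15:
- The mean of all differences is still τ, so there is no bias.
- The estimated variance becomes about 0.651² + π² × 30/29. For π = 0.2 this is 0.4232 + 0.0414 = 0.4646, an SD of 0.682.
- The true sampling variance of the mean is unchanged at 0.651²/30. Only the estimated standard error is too large, so the test is conservative.

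**3. Power and type I error at 15/15 without a period term (simulated).**

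| π (assumed) | Estimated SD | Power | Type I error |
|---|---|---|---|
| 0 | 0.651 | 81.3% | 5.0% |
| 0.1 | 0.658 | 80.7% | 4.7% |
| 0.2 | 0.682 | 78.7% | 4.1% |
| 0.3 | 0.719 | 75.0% | 3.1% |

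The simulated figures carry an uncertainty of a few tenths of a point. Putting the inflated SD straight into the power formula gives 77.6% at 0.2 and 73.2% at 0.3. That overstates the loss, because it treats the mean as more variable than it is.

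**4. With a period term (28 df).** Power is 81.2% whatever the period difference, and type I error is 5%. The cost is 81.3% − 81.2% = 0.1 percentage points.

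**5. Unequal sequences.** Bias without the term = π × (n1 − n2)/(n1 + n2). For π = 0.2:
- 16/14: 0.2 × 2/30 = 0.013 mEq/L, or 0.013/0.35 = 4% of the target.
- 15/10: 0.2 × 5/25 = 0.04 mEq/L, or 0.04/0.35 = 11% of the target.

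Simulation agrees, and the period-adjusted estimate is unbiased at both splits.

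**6. How likely is imbalance?** Blocks of 2 in two sex strata leave at most one unpaired allocation per stratum, so the initial split is no worse than 16/14. A 15/10 split from 15/15 needs five losses, all from one sequence. If loss is unrelated to sequence, the probability is 2 × C(15,5)/C(30,5) = 2 × 3,003/142,506 = 4%.

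**The case against.** The strongest reply is that silence is not exclusion. The article says that sex will be in the model. It does not say that nothing else will be, the paired-comparison wording is a parenthesis, and a full list of model terms commonly sits in an analysis plan. This stands in part: the article does not rule period out. But it chose to characterise the model and to name a covariate, and read as written that model has no period term.

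Several stronger readings are tempting and are not supported:

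- *A period difference is built into the design.* The response is taken after six weeks on each diet. Different starting conditions matter only if they persist that long, and nothing in the article shows that they do. The statement on deliveries, "Contents may vary throughout the intervention period based on price and availability", describes calendar variation. With enrolment planned at one participant a week over thirty weeks, one person's first period overlaps another's second.
- *Leaving out sequence does harm.* Sequence, like sex, is constant within a person and does not change the complete-pair diet estimate.
- *The omission inflates false positives.* At 15/15 the type I error falls. Even at 15/10 it is 4.8% for a period difference of 0.2.
- *The response is undefined.* Statistical methods settles on period endpoints and plans no change-score analysis. Objectives and Outcomes need only their wording aligned.

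It is also fair that the assumed differences of 0.2 and 0.3 are large beside the 0.35 target, and that at 0.1 almost nothing is lost. If 0.46 were itself the SD of the differences, power would be about 98% and would fall only to 97.0% and 95.1% at 0.2 and 0.3. That reading does not match the stated 80%, however.

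**Conclusion.** The point holds as a modest, nearly free improvement to the stated model. As described, the primary analysis includes a factor that cannot affect the within-person contrast and does not name the one design factor that can.

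The consequence is conditional on a period difference whose size the article does not give. With equal sequences there is no bias. Power drops by about 0.6, 2.6 and 6.3 percentage points (81.3% minus 80.7%, 78.7% and 75.0%) for assumed differences of 0.1, 0.2 and 0.3 mEq/L, and the latter two fall below the stated 80%. With unequal sequences the bias is small at 16/14 and reaches 0.04 mEq/L (period difference 0.2) only in an extreme 15/10 split. A reader might infer that the trial's estimate is already compromised. The documents do not support that.

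These figures assume complete pairs, 0.46 as a within-subject SD, a two-sided 5% test and no carryover.

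**What to change.** In Statistical methods, state the primary model as serum potassium at weeks 8 and 16, with fixed effects for diet, period and sex and a random participant effect. A sequence term may be added by convention but is not needed for the diet estimate. Use the same model structure for the secondary outcomes. Align the hypothesis under Objectives and the primary outcome under Outcomes with serum potassium at the end of each intervention period. Weeks 0, 1–2 and 10 can remain as measurement times, but they are not treatment endpoints.

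The cost is one degree of freedom and some wording; no new data are needed. A period term does not remove unequal carryover. Only the standard-first sequence changes diet at the start of period 1, so the text should not present the term as dealing with that.

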### Criteria for discontinuing or modifying allocated interventions

Each participant has the right to withdraw from the trial at any time. Participants may discontinue trial participation at any time and are requested to contact a research team member to inform them of their decision. In addition, the Investigator may discontinue a participant from the trial at any time if the investigator considers it necessary for any reason including:

Pregnancy.Ineligibility.Significant protocol deviation.Significant non-compliance with the protocol.Disease progression which results in inability to continue with the protocol.Withdrawal of consent.Loss to follow-up.Significant elevated risk due to hyperkalemia.

Withdrawal will not result in exclusion of the data for that participant from analysis. As the primary analysis will be based on an intention-to-treat there will also be a completer only analysis performed. If the participant is withdrawn within the first two weeks of the trial they will be replaced. If the replacement participant is withdrawn there will be no subsequent replacement. The reason for withdrawal will be recorded in the case report form (CRF), if provided.

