### Relevant concomitant care permitted or prohibited during the trial

All participants enrolled in the study will continue to receive multidisciplinary CKD care during and after the trial. Patients that are already on potassium binding therapy will be excluded from this trial. If it is determined that a participant needs to start potassium binding therapy they will be withdrawn from the trial and the reason for withdrawal will be recorded.

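### The rule excluding participants with missing values contradicts the intention-to-treat commitment and, taken literally, turns the primary analysis largely into the Completers analysis

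*Protocol article*

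**What the plan says.** All quotes are from the Protocol article.

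- Statistical methods, analysis sets: "The primary analysis will be conducted using the All Participants (intent to treat) analysis set", followed by "The primary analysis will be repeated in the Completers analysis set".
- Statistical methods, model: a linear mixed-effects model for repeated measures, described as "essentially a paired comparison of the endpoints of the standard care dK diet versus the experimental dK diet".
- Statistical methods, missing data: "Missing values will not be imputed unless otherwise noted", then "Analyses will exclude data from participants who have missing values for any variable required for the analysis". The model-checking sentence also promises checks "through sensitivity analyses regarding missing value strategies", without saying which.
- Criteria for discontinuing or modifying allocated interventions: "Withdrawal will not result in exclusion of the data for that participant from analysis". The same paragraph calls the primary analysis intention-to-treat and adds a separate completer-only analysis. Its list of reasons for which the investigator has discretion to discontinue a participant includes raised risk from hyperkalaemia.
- Relevant concomitant care: "If it is determined that a participant needs to start potassium binding therapy they will be withdrawn from the trial". This one is not discretionary.
- Outcomes: sK is scheduled at weeks 0, 1–2, 8, 10 and 16, so the period endpoints are weeks 8 and 16.

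**The concern.** Two statements about the same people cannot both be followed. Someone withdrawn in period 2 has a week 8 value but may have no week 16 value. One section keeps that person's data and the other removes the person.

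If the removal rule is applied, three things follow. The All Participants analysis and the Completers analysis use nearly the same people, so agreement between them is no reassurance. Valid period-1 endpoints are thrown away, although the planned mixed model could use them. And because one withdrawal route is tied directly to potassium, those removed may be the ones with high sK. If the liberalised diet does raise sK, more of them would be lost after that diet, and the estimated rise would be too small. The objectives include the safety of liberalisation, so this is the direction that matters. Choosing between the two sections once the data are in hand would be a data-driven choice.

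**Working it through.** **1. The text.** A paired comparison needs both endpoints. With no imputation and exclusion at participant level, the analysable set is those with sK at week 8 and at week 16. Apart from people who finish the trial but miss a blood sample, that is the Completers set. Withdrawals in the first two weeks fall in the run-in, before randomisation, and are replaced; they do not enter this argument.

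**2. The plan's power figure.** Inputs from Sample size: n = 30, difference 0.35, within-subject SD 0.46. Two-sided alpha of 0.05 is assumed, since sidedness is not stated.

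- SD of a paired difference = 0.46 × √2 = 0.651.
- Standard error with 30 pairs = 0.651/√30 = 0.119; noncentrality = 0.35/0.119 = 2.95.
- Paired t-test power (noncentral t, 29 df) = 81.3%. The stated 80% is reproduced, and 30 is the smallest number of pairs that reaches it.
- With fewer complete pairs: 28 gives 78.4%, 27 gives 76.8%, 24 gives 71.4%.

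**3. Bias when loss follows a high period-1 endpoint.** The documents give no withdrawal threshold or rate, so everything here is assumed except the screening range and the SD of 0.46. Assumptions: population mean sK 5.0, between-person SD 0.3, screening sK selected to 4.9–5.5 (Eligibility criteria), true rise 0.35, half of participants in each sequence. The within-person SD is 0.46 as stated, or 0.46/√2 = 0.325 if the stated figure is really the SD of the difference. A person whose week 8 value exceeds the cut-off is withdrawn and has no week 16 value. The cut-offs are illustrative and are not clinical proposals.

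| Within-person SD | Assumed cut-off (mEq/L) | Lost | Complete-pair estimate |
|---|---|---|---|
| 0.325 | 6.0 | 4.4% | 0.335 |
| 0.325 | 5.8 | 10.7% | 0.325 |
| 0.46 | 6.0 | 8.3% | 0.322 |
| 0.46 | 5.8 | 15.2% | 0.313 |

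These pool all remaining pairs. Giving the two sequences equal weight, as an analysis adjusted for period does, the range is 0.334 to 0.305. The shortfall is then (0.35 − 0.334)/0.35 = 5% to (0.35 − 0.305)/0.35 = 13%.

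A likelihood analysis that keeps the week 8 value of those withdrawn gives 0.350 to 0.352 in the same scenarios. With no true difference and the same cut-off on both diets, the complete-pair bias is zero.

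**4. Bias when loss comes before the endpoint is measured.** Suppose unscheduled tests lead to withdrawal and the liberalised endpoint itself is missing for the highest 5%, 10% or 20% (assumed mean 5.1, between-person SD 0.2–0.4, within-person SD 0.46). The complete-pair estimate is then too low by 0.04–0.05, 0.07–0.08 or 0.12–0.15. A likelihood model keeping the other endpoint does not cure this: its bias runs from −0.05 to −0.19.

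**The case against.** The strongest defence is that the plan already has the right ingredients: a mixed model, an intention-to-treat set kept separate from Completers, a statement that withdrawal does not remove data, and a promise of missing-value sensitivity analyses. With one row per endpoint, the exclusion sentence could be meant to drop only the incomplete record. That reading is possible, but the sentence excludes data from participants rather than records, and nothing says which section prevails. The sensitivity analyses are unspecified and would not change the primary rule.

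Some stronger inferences are tempting and are not supported.

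- *Hyperkalaemia forces withdrawal.* Only a binder start does. Discontinuation for hyperkalaemia risk is at the investigator's discretion.
- *The result is biased towards no harm.* This holds only if the diet raises sK or if triggers differ between diets. What attenuation would mean for the conclusion is also unsettled, because the Objectives state non-inferiority without a margin and Trial design says superiority.
- *The bias is 10 to 27%.* Deleting a pair whenever either endpoint exceeds 5.8–6.0 gives estimates of 0.316 to 0.255. But week 16 is the end of the trial, and a high value there cannot cause its own loss.

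The run-in also helps. Everyone takes the liberalised diet before randomisation, with a safety check, so some strong responders leave before they can affect the comparison. If run-in sK must stay at or below 5.5 (one reading of the eligibility and safety-assessment text), the shortfall falls to about 3 to 10% (estimates 0.340 to 0.316, loss 2 to 12%).

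**Conclusion.** The contradiction is real and stands on the page. Followed literally, the primary analysis largely becomes the Completers analysis and discards observed period-1 endpoints. The resulting bias is conditional and, in the scenario that fits the visit schedule, modest: about 5 to 13% of an assumed 0.35 mEq/L rise with 4 to 15% lost. It is nil if the diet has no effect and triggers are equal. It could be larger if unscheduled tests lead to loss before an endpoint is measured. The loss of power is more certain: the design has no spare pairs, and any exclusion takes it below 80% on the t-test. The sizes rest on assumed thresholds and sK distributions, because the documents give no withdrawal rate or threshold. The conflict in wording does not depend on those assumptions.

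**What to change.** - Reconcile the two sections by removing the participant-level exclusion for the primary and secondary mixed models. Fit the model by REML to all randomised participants with at least one post-randomisation period endpoint, keeping single-period data.
- Because that does not cure loss before an endpoint is measured, prespecify two sensitivity analyses. One uses the last sK before withdrawal or binder start as that period's endpoint. The other sets missing liberalised-period values progressively higher until the conclusion changes. Using the triggering value is a choice of estimand and selects an extreme reading, so it belongs here and not in the primary analysis.
- Report withdrawals for hyperkalaemia or binder start by diet.

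The cost is a change of wording and slightly more analysis. Clinical chemistry may be taken from nephrology clinic records, so a last sK should usually be retrievable. No clinical withdrawal rule changes. The choice should be fixed before the data are analysed.
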